### Criteria

2.5

#### Inclusion criteria

2.5.1

Participants will be included if they fulfill the following conditions:

(1)Satisfy the diagnostic criteria of CSM, and have definite spinal cord compression on MRI of cervical vertebrae^[13]^(2)Aged 18 to 80 years(3)Will be receiving surgical treatment (including anterior and posterior)(4)Sign informed consent

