### Sample size calculation

2.4

On the basis of the comparison treatment, we calculated the sample size of the 2 groups (Qishe pill versus Methycobal), which will be randomly distributed in an equal manner. Since Japanese Orthopaedic Association (JOA) scores can include sensory and motor function of the limbs and bladder, we chose JOA scores to calculate the sample size with an estimated correlation coefficient of the measurements of ρ=0.8 and with an alpha = 0.05. The JOA score was 13.68 ± 1.83 at the 6-month follow-up after oral administration of Methycobal, and 15.65 ± 1.61 at the 6-month follow-up after oral administration of traditional Chinese medicine for promoting blood circulation and removing blood stasis, so the calculated sample size of each group is 132. Considering a 20% loss to follow-up, the total sample size needed to detect this difference at a 5% level of significance with a power of 90% is 330 patients.

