### Randomization and allocation

2.6

We will randomize all included patients using a table of random numbers. The 288 patients will be randomly divided into the experimental group and the control group in a 1:1 ratio according to the treatment order.

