### Statistical analysis

2.12

Statistical analysis includes statistical description and statistical inference. The statistical description of quantitative index includes mean, standard deviation, median, minimum, and maximum. The qualitative index is described by frequency table and composition ratio. Statistical inference includes interval estimation and hypothesis testing.

All statistical analysis will be conducted by Statistical Packages of Social Sciences software (version 22.0). By the bilateral test, *P* < .05 will be considered to be statistically significant. The mean ± standard deviation will be used for the description of continuous variables. Continuous variables following the normal distribution will be analyzed by Student *t*-test. The non-normally distributed data will be tested using the rank sum test. The non-grade data in the counting data will be tested with the 2 test or the non-parametric test. The grade data will be checked by Ridit.

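### Both surgical approaches are eligible, but the stated allocation and tests make no use of approach: a small, cheap gain in precision is left unused

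*Protocol article*

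**What the plan says.** Three places in the protocol article bear on this.

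- **Section 2.5.1, Inclusion criteria.** Candidates for either operation are eligible: "Will be receiving surgical treatment (including anterior and posterior").
- **Section 2.6, Randomization and allocation.** "We will randomize all included patients using a table of random numbers"; patients are then "randomly divided into the experimental group and the control group in a 1:1 ratio according to the treatment order". No stratification factor is named, neither approach nor hospital.
- **Section 2.12, Statistical analysis.** "Continuous variables following the normal distribution will be analyzed by Student" t-test, and "The non-normally distributed data will be tested using the rank sum test". Neither test, as stated, takes a covariate or a stratum.

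The anterior/posterior distinction is not mentioned again as a stratum, covariate or subgroup. The article reports no expected mix of approaches and no outcome by approach.

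**The concern.** Every patient has an operation, and the Introduction credits surgery with relieving compression and improving function. The outcomes in section 2.7 (JOA, VAS, NDI and cord measurements on MRI) are ones that surgery could be expected to influence. If patients operated on from the front and from the back recover differently, that difference adds to the spread within each arm, and a two-group test treats it as noise.

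Planned approach is a pre-treatment characteristic that should be on record for every patient, so it could be used for balance and adjustment without new data. What is at stake is the width of the confidence interval for the treatment difference, not its validity.

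**Working it through.** **The plan's own figures.** Section 2.4 gives JOA 13.68 ± 1.83 with the control drug and 15.65 ± 1.61 with the comparator herbal treatment, both at 6 months, and 132 per group before 20% loss.

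- Difference: 15.65 − 13.68 = 1.97.
- Pooled SD: √((1.83² + 1.61²)/2) = √2.97 = 1.72.
- Loss to follow-up: 132/0.80 = 165 per arm, 330 in total. This step reproduces.
- The 132 itself does not follow from these inputs: the usual two-sample formula (two-sided 5%, 90% power) gives 17 per group. That is a separate matter; 132 and 165 are used here only as the planned sizes.

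The plan has no figure for approach, so two quantities are **assumed**: posterior share p = 0.5, and JOA gap between approaches g = 0.5 to 1.0 points. The SD of 1.72 is taken as the total within-arm SD.

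**Step 1. Share of JOA variance due to approach** = p(1−p)g²/SD².

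- g = 0.5: 0.25 × 0.25/2.97 = 2.1%.
- g = 1.0: 0.25 × 1.00/2.97 = 8.4%.
- g = 0: 0%.
- Wider assumptions: p = 0.2 with g = 0.5 gives 0.16 × 0.25/2.97 = 1.3%; p = 0.5 with g = 1.5 gives 0.25 × 2.25/2.97 = 18.9%.

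**Step 2. Chance imbalance in approach**, 165 per arm.

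- SE = √(2 × 0.25/165) = 0.055, or 5.5 percentage points.
- 95% range: 1.96 × 0.055 = ±0.108, about ±11 points.
- In JOA points: 0.108 × 0.5 = ±0.05, up to 0.108 × 1.0 = ±0.11. These are 95% ranges, not maxima.
- Section 2.6 gives 288 patients rather than 330. With 144 per arm the range is 1.96 × √(0.5/144) = ±11.5 points, so the conclusion does not turn on that discrepancy.

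**Step 3. Are steps 1 and 2 separate harms?** No.

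- SE of the treatment difference: 1.72 × √(2/165) = 0.19.
- Its component from approach imbalance at g = 1.0: 0.055 × 1.0 = 0.055.
- Squared ratio: (0.055/0.19)² ≈ 8.4%, the same share as in step 1.

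The ordinary standard error already contains the imbalance.

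**Step 4. What adjustment would buy.**

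- The SE is multiplied by √(1 − 0.021) = 0.99 to √(1 − 0.084) = 0.96, so intervals narrow by about 1% to 4%.
- At the planned 1.97 points, power with 132 per arm exceeds 99.9% with or without adjustment.
- The difference that 132 per arm detects with 90% power is 1.72 × (1.960 + 1.282) × √(2/132) = 0.69 points. There, adjustment raises power to 90.6% (g = 0.5) or 92.3% (g = 1.0). Equivalently, 130 or 121 per arm would suffice instead of 132.

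**The case against.** The best case for leaving the plan alone has four parts.

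1. **This may be silence rather than choice.** The article is condensed and the analysis plan is not shown. Section 2.12 lists tests by data type and does not rule out adjustment, and a random-number table can also produce stratified lists. This stands in part: it cannot be said that stratification or adjustment is excluded. But the article does name an allocation method and tests, and as named they make no use of approach.

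2. **Nothing shows that approach is prognostic.** That surgery helps does not mean the two approaches give different results, and the Abstract lists residual symptoms without splitting them by approach. This stands. The gap g is an assumption, and zero is possible.

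3. **Chance imbalance is not confounding.** A reader might infer that an uneven mix of approaches would bias the estimated drug effect or undermine the test. The documents do not support that: allocation is random, so the estimate is unbiased on average, the type I error holds, and step 3 shows that the imbalance is already inside the standard error. Nor do they show that the two hospitals differ in their mix. This stands in full.

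4. **It is immaterial at the planned effect.** A ±0.05 to ±0.11 point range is about 3% to 6% of 1.97, and power is unchanged. This also stands, although 1.97 comes from a different herbal treatment, so a smaller true effect is possible, and section 2.4 states no power for the secondary outcomes.

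It is also fair to say that baseline JOA may matter more. If the ρ = 0.8 in section 2.4 is a baseline-to-follow-up correlation, which the article does not say, adjusting for baseline would leave 1 − 0.8² = 36% of the variance. Approach could then add less or more than step 1 suggests, depending on how far it is related to baseline severity.

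**Conclusion.** The point holds as an optional improvement in precision, not as an error in the design. Under the stated assumptions (50:50 mix, gap of 0.5 to 1.0 JOA points, within-arm SD 1.72), leaving approach out forgoes about 2% to 8% of JOA variance. Under the wider assumptions the range is 1% to 19%, and it is near 0% if approach does not predict outcome. No conclusion about a 1.97-point difference would change. The benefit is confined to smaller true effects and to VAS, NDI and the MRI measures, for which the size of any approach effect cannot be worked out from the article. Priority is low, but so is the cost.

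**What to change.** Before comparative data are seen, pre-specify a linear model for JOA with treatment, planned surgical approach (anterior or posterior) as a fixed factor, and baseline JOA. Include approach in the same way in the VAS, NDI and MRI comparisons, using a model suited to the scale of each outcome. Use the planned rather than the performed approach, so that the factor is fixed before allocation.

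If randomisation has not begun, also stratify the list by planned approach. If it has begun, leave the allocation as it is and add the model term only.

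Cost: two random lists to administer instead of one, and one extra model term, a single degree of freedom among about 264 to 330 patients. No additional patients, visits or measurements are needed. If approach turns out not to be prognostic, almost nothing is lost.

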**Methods/design::**

A multicenter, randomized controlled clinical trial will be conducted to evaluate the efficacy and safety of the Qishe Pill. A total of 330 patients with CSM who receive surgical treatment will be randomly divided into 2 groups, treated for 12 weeks and with a 1-year follow-up. The primary outcome will be Japanese Orthopaedic Association score from the baseline to 4 weeks, 12 weeks, 24 weeks, and 48 weeks after surgery. Secondary outcomes will include Visual Analogue Scale score, Neck Disability Index, and imaging indicators (including magnetic resonance imaging and X-ray). Additionally, adverse reactions will be observed and recorded as safety indicators.

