**Discussion::**

Although the Qishe pill can effectively improve the discomfort of the neck and upper limbs in clinical applications, there is a lack of clinical research on postoperative patients. This study will investigate the efficacy and safety of the Qishe pill in treating postoperative symptoms of CSM.

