## Introduction

1

Cervical spondylotic myelopathy (CSM) often presents with symptoms that are related to dysfunction of the spinal cord, caused by the degeneration of the cervical vertebrae (such as intervertebral disc, ligaments, osteophytes) and related secondary changes (excessive activity of the cervical vertebrae and cervical instability).^[1,2]^ By age 50, magnetic resonance imaging (MRI) showed that as many as 31.6% of the population had spinal cord compression, rising to 66.8% after age 80.^[3]^ Progressive CSM can cause a range of symptoms such as limb numbness, walking instability, and bundle sensation, and 20% to 60% of spinal or neurological symptoms can worsen without surgery.^[4,5]^ Therefore, an increasing number of patients are receiving surgical treatment because it can relieve nerve compression, stop the progression of nerve damage, and improve function and quality of life. Although surgery is usually safe and effective, complications occur in 11% to 38% of patients. Fehlings et al^[6]^ found that overall perioperative and delayed complication rates were 15.6% and 4.4%, respectively. Most complications are temporary and non-neurological. No invasive intervention or prolonged hospital stay is required. However, some patients have intractable neck pain, limb numbness, and even muscle weakness after surgery.^[7,8]^

The Qishe pill is a Chinese medicine consisting of processed Radix Astragali, Muscone, Szechuan Lovage Rhizome, Radix Stephaniae Tetrandrae, Ovientvine, and Calculus Bovis Artifactus, and has the function of regulating qi and promoting blood circulation, regulating collaterals, and relieving pain.^[9,10]^ Related studies showed that it can effectively relieve cervical pain and numbness, and improve quality of life in patients with CSM.^[11,12]^ It has been found in clinical practice that the Qishe pill can improve postoperative symptoms of CSM to some extent, but there is still a lack of evidence to prove this. Therefore, we designed a multicenter, randomized, clinically controlled trial to demonstrate its efficacy and safety.

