**Figure 2 F2:**
[figure not shown]
Measurement of percentage of median sagittal spinal cord compression in T2WI. T2WI = T2 weighted image.

(1)Compression Ratio (Fig. 3): compression ratio is the ratio of anteroposterior (AP) to laterlateral (LL). AP is the anterior and posterior diameter of the spinal cord at the level of the most severe spinal cord compression on the horizontal axis of T2WI, while LL is the left and right diameter.(2)Transverse Area (Fig. 4): The cross-sectional area of the most severely compressed spinal cord on T2WI will be measured.

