## Discussion

3

Patients with CSM have a high rate of surgery, and some patients have obvious residual symptoms.^[19]^ In the absence of established guidelines, treatment should center around relief of patient symptoms. Treatment modalities include bed rest, medications, physical exercise, thermal therapy, and others.^[20,21]^ Therefore, it is important to explore new treatment options to alleviate postoperative symptoms and improve the quality of life of patients. To the best of our knowledge, this is the first randomized controlled clinical trial to investigate the efficacy of the Qishe pill in the treatment of postoperative residual symptoms of CSM.

The Qishe pill is a combination of eight herbal ingredients and has been widely used in the clinical setting, and can significantly reduce the stiffness and numbness of the neck and shoulder. It is recommended for treating a variety of ailments, including neck pain, radiating pain, limb stiffness and numbness, weakness, fatigue, and other symptoms. Related studies have proven that astragalus and chuanxiong have the effects of nourishing qi, generating blood, and improving circulation.^[22,23]^ However, there remains a lack of evidence for the residual neck and shoulder pain and numbness of CSM. Therefore, this clinical study will be conducted to explore the efficacy and safety of the Qishe pill to provide a new therapeutic scheme for clinical improvement of postoperative residual symptoms of CSM.

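### Eligibility is set before surgery with no check for residual symptoms, and baseline is not placed relative to surgery, so the trial estimates an effect in all operated patients, not in those with residual symptoms

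*Protocol article*

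**What the plan says.** **Aim.** The abstract says: "This study will investigate the efficacy and safety of the Qishe pill in treating postoperative symptoms of CSM". Section 3 (Discussion) is narrower: the trial is to "investigate the efficacy of the Qishe pill in the treatment of postoperative residual symptoms of CSM".

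**Who has the target condition.** The Introduction reports that "some patients have intractable neck pain, limb numbness, and even muscle weakness after surgery". The abstract's Background, the VAS item in section 2.7.2 and section 3 likewise attribute postoperative symptoms to some patients only. No proportion is given.

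**Who is enrolled.** Section 2.5.1 lists four criteria: CSM in patients who "have definite spinal cord compression on MRI of cervical vertebrae", age 18 to 80, "Will be receiving surgical treatment (including anterior and posterior"), and consent. The exclusions in section 2.5.2 say nothing about symptoms after the operation.

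**What is measured, and from when.** The abstract gives the primary outcome as the JOA "score from the baseline to 4 weeks, 12 weeks, 24 weeks, and 48 weeks after surgery". Section 2.7.1 adds the JOA improvement rate. Section 2.10 schedules a baseline visit and visits at weeks 4, 12, 24 and 48, with 12 weeks of intervention and 36 of follow-up. Section 2.12 compares normally distributed continuous variables by Student t-test.

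**The concern.** A patient who recovers fully after decompression meets every stated criterion. The enrolled population is therefore everyone operated on for CSM, while the conclusion in section 3 is about those left with symptoms. If the drug works only in the latter, the estimated effect is an average over patients who can and cannot benefit. A null result would not show failure in residual symptoms, and a positive one would not be specific to them.

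The undefined baseline adds a second difficulty. Eligibility is worded before surgery and the outcome runs to weeks after surgery, so a reader may take baseline as preoperative. In that case the reported change and improvement rate in each arm would be largely a description of the operation.

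**Working it through.** **1. Aim against eligibility.** Target: residual symptoms after surgery (section 3), present in some patients (Introduction). Selection: four criteria, all assessable before surgery (section 2.5.1). No later step in the text narrows the population. The two do not match, and this does not depend on where baseline lies.

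**2. Baseline.** Let P be the preoperative JOA, B the JOA after surgery but before the first dose, and Y the JOA at a follow-up visit.

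- If baseline is P: change = Y − P = (B − P) + (Y − B). The first term precedes any drug. Randomisation gives it the same expectation in both arms, so the difference between arms is not biased, but each arm's mean change and improvement rate contain it.
- If baseline is B: change = Y − B, which is recovery during treatment and follow-up.

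The text does not say which applies. The abstract counts weeks after surgery. In section 2.10, 12 + 36 = 48 weeks fits a clock started at treatment. The interval between surgery and first dose is not stated, so these need not be the same day zero.

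**3. The plan's own sample size.** Inputs from section 2.4: means 13.68 and 15.65, SDs 1.83 and 1.61, alpha 0.05, power 90%. The test is two-sided (section 2.12).

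- Difference: 15.65 − 13.68 = 1.97.
- Pooled SD: √((1.83² + 1.61²)/2) = 1.72.
- n per group = 2 × 1.72² × (1.96 + 1.28)² / 1.97², which rounds up to 17.

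The stated 132 per group does not follow from these inputs; using ρ = 0.8 as well gives 4 to 14, depending on the variant. The dropout step does reproduce: 132/0.8 = 165 per group, 330 in total. The mismatch is a separate matter. Here 132 per group is taken as given.

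**4. Does dilution cost power?** Assume the full 1.97 points occurs only in a share f of patients, none in the rest, and the SD is unchanged. The documents do not give f. The standard error of the difference is 1.72 × √(2/132) = 0.212, and power ≈ Φ(1.97f/0.212 − 1.96).

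| f | All-patient difference | Power at 132 per group |
|---|---|---|
| 0.75 | 1.48 | >99% |
| 0.50 | 0.99 | 99.6% |
| 0.40 | 0.79 | 96% |
| 0.30 | 0.59 | 80% |
| 0.20 | 0.39 | 46% |

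The difference detectable with 90% power is (1.96 + 1.28) × 0.212 = 0.69 points, so the break-even share is 0.69/1.97 = 0.35. If the mixture also widens the experimental arm, adding f(1 − f) × 1.97² to its variance, break-even moves to about 0.375: average variance 2.97 + 0.45 = 3.43, SD 1.85, detectable difference 0.74 = 1.97 × 0.375. The picture is the same.

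**5. Precision of a residual-symptom contrast.** With 132f per group, the difference detectable at 90% power is 0.69/√f: 0.97 points at f = 0.5 and 1.26 at f = 0.3. Both lie below 1.97, but both are coarser than the 0.69 available in all patients.

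**The case against.** Enrolling all operated patients is a legitimate design, and the abstract's aim refers to postoperative symptoms without the word residual. JOA, VAS and Neck Disability Index are all scored after surgery, so residual symptoms are observed even though they are not selected for. That patients without them cannot benefit is an assumption. The planning figures hint at wide room for benefit: (15.65 − 13.68)/1.83 = 1.08, so if scores are roughly normal about 86% of controls lie below the experimental mean, although how those source populations were selected is not stated. All of this stands. It shows that the design can answer a question, but the question is not the one in section 3.

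A preoperative baseline is indeed only an inference. Section 2.5.1 fixes who is eligible, not when baseline is scored; the abstract does not say whether randomisation comes before or after the operation; and Table 1 and Figure 1, which could settle it, are not shown. The point is therefore conditional.

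Nor is surgical recovery shown to add noise. Section 2.4 sizes the trial on the 6-month score, not on change, and a comparison of follow-up scores does not depend on the baseline. If ρ = 0.8 applied to baseline and follow-up, a change score would have 2 × (1 − 0.8) = 0.4 times the variance of a single score. The protocol does not say which measurements ρ relates.

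A reader might also object that the MRI measures move to a different level after decompression. Section 2.7.2 defines how to measure at the most compressed level; it does not say the level is chosen afresh at each scan. Such reading rules commonly sit in the full protocol, so no fault is claimed there.

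**Conclusion.** The mismatch between aim and population holds on the text alone. As written, the trial estimates the effect of the Qishe pill against Methycobal in all patients after surgery for CSM, possibly diluted, and cannot by itself support a conclusion about residual symptoms. The baseline point holds conditionally: the text leaves it open, and if it is preoperative the JOA change and improvement rate mix decompression with drug.

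Three stronger readings are tempting, and the documents do not support them:

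- **Bias between arms.** Both arms are operated on and randomised, so surgical recovery is common to them.
- **An underpowered trial.** At the planned 1.97 points and 132 per group, power falls below 90% only if fewer than about 35% of patients can benefit. Starting instead from the 0.69 points that gives exactly 90% power would guarantee a shortfall for any share below 1, and the protocol does not plan for that effect.
- **A low share with residual symptoms.** The Introduction's 11% to 38% are surgical complication rates, and it calls most complications temporary and non-neurological. They are not the share with residual symptoms.

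The power statement rests on the section 2.4 means and SDs, no effect outside the share f, and an unknown f.

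**What to change.** 1. Define baseline JOA, VAS and Neck Disability Index as the postoperative assessment before the first dose, scored without knowledge of allocation. State one day zero and count all visits from it, so that the abstract and section 2.10 use the same clock.
2. Keep the preoperative JOA and analyse follow-up JOA adjusted for it and for the postoperative pre-dose score, in place of the unadjusted t-test. If ρ = 0.8 holds between such a score and follow-up, adjustment for that one score alone reduces the residual variance to 1 − 0.8² = 0.36 of the unadjusted value.
3. Prespecify a supportive week-24 contrast in patients with residual symptoms at that baseline, by a threshold the sponsor fixes in advance, and state that it has less power than the all-patient comparison.
4. Word the all-patient conclusion, and the aim in section 3, as applying to patients after surgery for CSM.

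The cost is protocol wording, one short extra scoring of three scales during the surgical stay, and a supportive subgroup result with less precision. Nothing changes in treatment, imaging or sample size.
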